### Interventions

Figure 2 summarizes the experimental paradigm. Trained physical therapists administer interventions and assessed outcomes. Compliance with the interventions is monitored by one of the researchers. If a subject misses a session, the researcher calls him/her or the caregiver, in order to ascertain reasons for the absence and reinforce the importance of adherence to the protocol. All interventions are administered in the morning and scheduled according to the best possible time to subjects and caregivers. Transportation costs are covered by the protocol. The Template for Intervention Description and Replication (TIDieR) Checklist is shown in Supplementary Table 1.

**Figure 2 F2:**
[figure not shown]
Experimental paradigm.

#### RPSS

Trains of electrical pulses (1 ms of duration for each) at a frequency of 10 Hz are delivered at 1 Hz (500 ms on, 500 ms off) by three pairs of surface electrodes (KendallTM) with a square pulse stimulator (Grass Instrument Division of Astro-med, Inc, Braintree, MA) (34, 35). A customized device (Alfamedic Ltda, Sao Paulo) provides independent outputs to the three nerves, with a maximum output voltage of 130 volts.

In the active group, RPSS is administered to the median, ulnar and radial nerves of the paretic arm in all sessions. In the sham group, RPSS is administered to the superficial peroneal, tibial, and sural nerves of the paretic leg, as previously reported (34, 35). In both groups, the duration of stimulation is 90 min.

The threshold and maximum intensity of stimulation to produce paresthesias in the territory of the stimulated nerves, in the absence of visible muscle contractions or pain are determined. The intensity is kept as the maximum that evokes paresthesias in the absence of finger movements or pain (5, 9, 35).

Subjects are comfortably seated and are kept at rest during RPSS. Every 5 min, they are asked about the sensations elicited by stimulation in order to raise attention to the stimulated body part. The intensity of stimulation is increased if intensity of paresthesias decreases, and is decreased if movements or pain are elicited during the 90-min period of RPSS. During RPSS, they watch a movie to avoid fluctuations in wakefulness/attention (36).

In active RPSS, the median nerve is stimulated between the tendons of the flexor carpi radialis and palmaris longus with the cathode positioned 2–3 cm proximal to the wrist. The ulnar nerve is stimulated radially to the flexor carpi ulnaris tendon, with the cathode 3–5 cm proximal to the wrist. The radial nerve is stimulated 4–6 cm proximally to the ulnar styloid process (37). In all subjects, the three nerves are stimulated.

In sham RPSS, the superficial peroneal nerve is stimulated medially and about 12 cm proximally to the lateral malleolus. The tibial nerve is stimulated posteriorly and proximally to the medial malleolus. The sural nerve is stimulated in the midcalf, about 10–14 cm proximally to the lateral malleolus. This strategy for sham stimulation has been previously described (34, 38).

Researchers involved in RPSS receive training prior to participation in the protocol. They do not participate in FES, motor training or evaluation of outcomes.

#### Functional Electrical Stimulation (FES)

Immediately after active or sham RPSS, FES is delivered by a trained occupational or physical therapist to the extensor digitorum communis muscle of the paretic arm with self-adhesive (3 × 5 cm) electrodes and a FESMED IIV stimulator (CARCI, São Paulo, Brazil) for 25 min, after 5 min of familiarization (32). Square biphasic pulses with duration of 250 μs with auditory pace (human voice) are delivered at 0.4 Hz. Subjects are comfortably seated with their trunk and upper limb stabilized with bands. They are instructed to extend the wrist every time they hear the sound of a human voice saying “now” and then relax. A goniometer is kept next to the wrist to maintain the reference of target range of the movement, defined by, at least, 10 degrees of wrist extension.

#### Motor Training

Task-specific training based on Constraint-induced Movement Therapy (CIMT) (39) is applied to the paretic arm for 45 min. Four shaping tasks are defined for each patient and two tasks are applied per day. The tasks are chosen by a trained therapist based on the motor potential for each patient. Motor training is provided in an individual basis to each subject.

Two behavioral strategies are applied in each session of treatment. First, participants are asked about performance of 15 items of the Quality of Movement Scale of the Motor Activity Log (MAL) (24) to reinforce the use and perception of the upper limb in daily life. Second, subjects are assigned 10 functional tasks to be performed daily at home with the paretic arm, for at least 30 min per day. The tasks can be changed according to individual progress.

In addition, a formal contract between the therapist and participant is presented and signed, so that subjects compromise to use their paretic upper limb in activities of daily living as much as possible in the real world, out of the therapeutic setting, as described in constraint-induced movement protocols (39).

### Familiarization

First, subjects are exposed to the interventions in a familiarization session. Either active or sham RPSS is administered, according to the randomization. FES is applied for 5 min.

Measurements of ROM of wrist extension and flexion, grip and pinch strength are performed until subjects reach a stable performance defined as a difference <20% between 3 consecutive measurements. Evaluation of all baseline outcomes is performed on the same day of the familiarization session.

### Outcome Measures

The primary outcome measure is the Wolf Motor Function Test (WMFT) (40) after 6 weeks of treatment (end of treatment). The average time to perform 15 functional tasks (maximum, 120 s per task; if >120 s, the score is 121 s) as well as the quality of movement (Functional Ability Scale; range, 0 to 5) are assessed. The Minimal Clinically Important Differences (MCID) in the chronic phase are 1.2 to 2 s for the average time to complete the tasks, and 0.2 to 0.4 points for the Functional Ability Scale (41). The WMFT is a valid instrument with high interrater and test-retest reliabilities, as well as high internal consistency (42). The original version of the WMFT was developed to assess the effects of CIMT in stroke and traumatic brain injury.

The secondary outcomes are the WMFT at 3, 10 and 18 weeks after beginning of treatment, as well as the following outcomes measured at 3, 6, 10, and 18 weeks after beginning of treatment: MAL; active range of motion (ROM) of wrist extension and flexion; grasp and pinch strength in the paretic and non-paretic sides (the order of testing is randomized within and across subjects); MAS; FMA-UL in the paretic arm; BI; SIS; Beck Depression Inventory Short Form. Measurements assessed after 3 and 6 weeks of treatment are scheduled for days other than those in which the patients receive treatment, in order to avoid fatigue.

In addition, ROM of wrist extension and flexion is measured before and after the first session of treatment. ROM of wrist extension and flexion is measured with an analogic goniometer (ISP® Instituto São Paulo, São Paulo, Brazil) (43). Averages of three trials are calculated. Grip strength is measured with a Jamar dynamometer (Saehan Jamar, Changwong Korea) and pinch strength, with a digital dynamometer (Kratos, São Paulo, Brazil) (44). The trunk and the arms are stabilized and the wrist is kept in a neutral position during measurements.

All outcomes are evaluated by trained researchers blinded to the type of RPSS administered to patients. Assessments are videotaped.

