## Abstract

**Background:** Repetitive peripheral nerve sensory stimulation (RPSS) has emerged as a potential adjuvant strategy to motor training in stroke rehabilitation. The aim of this study is to test the hypothesis that 3 h sessions of active RPSS associated with functional electrical stimulation (FES) and task-specific training (TST) distributed three times a week, over 6 weeks, is more beneficial to improve upper limb motor function than sham RPSS in addition to FES and TST, in subjects with moderate to severe hand motor impairments in the chronic phase (>6 months) after stroke.

**Methods:** In this single-center, randomized, placebo controlled, parallel-group, double-blind study we compare the effects of 18 sessions of active and sham RPSS as add-on interventions to FES and task-specific training of the paretic upper limb, in 40 subjects in the chronic phase after ischemic or hemorrhagic stroke, with Fugl-Meyer upper limb scores ranging from 7 to 50 and able to voluntarily activate any active range of wrist extension. The primary outcome measure is the Wolf Motor Function Test (WMFT) after 6 weeks of treatment. The secondary outcomes are the WMFT at 3, 10, and 18 weeks after beginning of treatment, as well as the following outcomes measured at 3, 6, 10, and 18 weeks: Motor Activity Log; active range of motion of wrist extension and flexion; grasp and pinch strength in the paretic and non-paretic sides (the order of testing is randomized within and across subjects); Modified Ashworth Scale; Fugl-Meyer Assessment-Upper Limb in the paretic arm; Barthel Index; Stroke Impact Scale.

**Discussion:** This project represents a major step in developing a rehabilitation strategy with potential to have impact on the treatment of stroke patients with poor motor recovery in developing countries worldwide. The study preliminarily evaluates a straightforward, non-invasive, inexpensive intervention. If feasibility and preliminary efficacy are demonstrated, further investigations of the proposed intervention (underlying mechanisms/ effects in larger numbers of patients) should be performed.

**Trial Registration:** NCT02658578.

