### Sample Size

We planned to include up to 40 patients and to determine the final sample size after evaluating the results of the first twenty patients included in the trial in regard to the MCID of the primary outcome (change in WMFT, Functional Ability Scale at 6 weeks compared to baseline).

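### The primary endpoint is stated inconsistently: two unranked WMFT scores under Outcome Measures, the Functional Ability Scale alone under Sample Size

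*Protocol article*

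**What the plan says.** The protocol article describes the primary outcome in three sections and uses it in a fourth.

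- **Abstract, Methods:** "The primary outcome measure is the Wolf Motor Function Test (WMFT) after 6 weeks of treatment". No score is named.
- **Outcome Measures:** "The primary outcome measure is the Wolf Motor Function Test (WMFT) (40) after 6 weeks of treatment (end of treatment"). Two scores follow. The first is a time: "The average time to perform 15 functional tasks (maximum, 120 s per task; if >120 s, the score is 121 s"). The second is a rating, introduced by "as well as the quality of movement (Functional Ability Scale; range, 0 to 5) are assessed". MCIDs are given for both: "1.2 to 2 s for the average time to complete the tasks, and 0.2 to 0.4 points for the Functional Ability Scale". A secondary list follows and contains the WMFT at 3, 10 and 18 weeks, so neither score at 6 weeks is placed among the secondary outcomes.
- **Sample Size:** this section says "We planned to include up to 40 patients and to determine the final sample size after evaluating the results of the first twenty patients". Those results are to be judged against the MCID of what it calls the "primary outcome (change in WMFT, Functional Ability Scale at 6 weeks compared to baseline"). Time is absent.
- **Data Analysis:** the repeated-measures ANOVA or GEE model names no WMFT score. The comparison of patients who reach the MCID refers to the WMFT without saying which score counts.

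**The concern.** A primary endpoint has to be one defined variable, or several with a stated rule for combining them. Here the section that defines outcomes lists two scores of equal standing, and the section that sets the sample size uses one.

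Two things are at stake. First, someone analysing the data could report either WMFT score as the primary result and cite the article in support. If that choice were made after seeing results, the false-positive rate for a primary claim would exceed the level of a single test. Second, the final sample size is to be decided from the first twenty patients against the MCID of FAS. If time were then reported as primary, the trial would have been sized on a different variable, with a different unit and a different MCID.

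**Working it through.** **Step 1: can the definitions be reconciled?**

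| Section | Score named as primary |
|---|---|
| Abstract | WMFT, score not named |
| Outcome Measures | WMFT; time and FAS both described, unranked |
| Sample Size | FAS change from baseline only |
| Data Analysis | score not named |

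If FAS is intended, the Abstract, Outcome Measures and Data Analysis are incomplete, and time at 6 weeks has no place in the outcome hierarchy. If both scores are intended, Sample Size is wrong. On either reading at least one section has to change.

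**Step 2: the plan's own figure.** The only sample-size figure is the ceiling of 40. The article gives no alpha, power or standard deviation with it, so it cannot be reproduced and does not show which score it was meant to serve.

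**Step 3: type I error if either score could count.** Inputs, all assumed because the document states none of them: two-sided 5% per score, success on either, and correlation ρ between the two test statistics from 0 to 0.95. The sign of ρ does not matter for two-sided tests, so it makes no difference that time falls as FAS rises.

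Formula: 1 − P(|Z₁| ≤ 1.96 and |Z₂| ≤ 1.96), with Z₁ and Z₂ bivariate normal with correlation ρ. For ρ = 0 this is 1 − 0.95² = 0.0975.

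| ρ | Type I error, either score at 5% | Either score at 2.5% (Bonferroni) |
|---|---|---|
| 0 | 0.0975 | 0.0494 |
| 0.5 | 0.0907 | 0.0465 |
| 0.7 | 0.0835 | 0.0430 |
| 0.8 | 0.0781 | 0.0402 |
| 0.9 | 0.0704 | 0.0362 |
| 0.95 | 0.0646 | 0.0330 |

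With one named primary score the figure is 0.05. The ratio to 0.05 runs from 0.0646/0.05 = 1.29 to 0.0975/0.05 = 1.95.

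**Step 4: why sizing on FAS does not carry over to time.** Take the ceiling of 40 at the stated 1:1 allocation, so 20 per arm, and assume two-sided 5%, 80% power, the normal approximation and complete data. The largest standard deviation at which a between-group difference δ is detectable is δ × √(20/2) / (1.96 + 0.84).

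| Score | δ (MCID) | Largest SD |
|---|---|---|
| FAS | 0.2 points | 0.23 points |
| FAS | 0.4 points | 0.45 points |
| Time | 1.2 s | 1.35 s |
| Time | 2 s | 2.26 s |

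Whether 40 is enough depends on two unrelated standard deviations, neither of which the article gives. A decision that 40, or fewer, suffices for FAS therefore says nothing about time.

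**The case against.** The strongest reply is that Sample Size already answers the question. It is the only place that defines a variable and not just an instrument, and a general statement followed by a specific one is naturally read as settled by the specific one. Outcome Measures may simply be describing how the test is scored. Much of this stands: FAS is the most natural reading, and the fix adopts it. It does not remove the inconsistency. The definition is a parenthesis in the sample-size section, the outcome section gives both scores an MCID under the primary outcome, and the secondary list leaves no place for time at 6 weeks.

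A second reply is that multiplicity rules belong in a full protocol or SAP that is not shown. That also stands, and the absence of an alpha split is not held against the article. Which variable is primary is a different matter, because the article itself states it in two ways that do not match.

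A third reply is that the study describes itself as a preliminary evaluation, with larger studies to follow. That lowers the consequence of an inflated error rate. It does not remove the need for one endpoint, since the sample-size decision depends on it.

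Two stronger readings are tempting, and the document supports neither.

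- A reader might infer that the trial may claim success on either score, at nearly double its stated error. No section calls the scores co-primary or says that either suffices, and no error rate is stated. Near-doubling also needs near-independence, the least plausible case for two scores of one test.
- A reader might infer from the 121 s cap that mean time is unsuitable in these patients. The article gives no distribution of WMFT times and no frequency of timed-out tasks, and Data Analysis already lets the model depend on the distribution of the data.

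**Conclusion.** The concern holds as an inconsistency in the definition of the primary endpoint. Two unranked scores sit under it in Outcome Measures, FAS change alone is named in Sample Size, and no score is named in the Abstract or Data Analysis. A choice between the scores is not excluded, though nothing in the article permits it either.

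The size is conditional. If each score were tested at two-sided 5% and either could count, the type I error would be about 6.5% at correlation 0.95 and 9.75% under independence, instead of 5%. The alpha, the correlation and the either-score rule are all assumptions. The possible mismatch between the FAS-based sample-size decision and the reported endpoint is likewise a risk left open, not something the article plans.

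**What to change.** In the Abstract and Outcome Measures, name FAS change from baseline at 6 weeks as the single primary endpoint, as Sample Size does. List WMFT time at 6 weeks among the secondary outcomes. In Data Analysis, say that the primary comparison is on FAS and that the WMFT responder comparison uses FAS. As the FAS MCID is given as a range of 0.2 to 0.4 points, the value that defines a responder can be stated in the same sentence.

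If both scores are meant to be primary, correct Sample Size instead and test them in a fixed sequence, FAS first, or with Holm. Either procedure keeps the overall error at or below 5%.

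The cost is wording only. The downside is that, with FAS as the single primary, a benefit on time alone could no longer be called a primary success. Under the fixed sequence, time could be tested as primary only after FAS had succeeded. Under Holm, the first test would be held to 2.5%. The change should be made and dated before group comparisons are seen, with a note on whether the evaluation of the first twenty patients had already taken place.

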### Adverse Events

Questions about adverse events are asked immediately after each session of RPSS and FES. Subjects are also instructed to spontaneously report any adverse events throughout the protocol.

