Six hours of daily rehabilitation for 10 days over 2 weeks may not be a feasible strategy in developing countries where the greatest disability from stroke occurs (12). Here, we report the design of the study “Peripheral Nerve Stimulation and Motor Training to Enhance Hand Function After Stroke” (ClinicalTrials.gov identifier NCT02658578). The aim of this study is to test the hypothesis that 3-h sessions of active RPSS associated with functional electrical stimulation (FES) and task-specific training (TST) distributed three times a week, over 6 weeks, is more beneficial to improve upper limb motor function than sham RPSS in addition to FES and TST, in subjects with moderate to severe hand motor impairments in the chronic phase after stroke.

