## Methods and Analysis

### Design

In this single-center, randomized, placebo controlled, parallel-group study we compare the effects of 18 sessions of active and sham RPSS as add-on interventions to FES and task-specific training of the paretic upper limb, in subjects in the chronic phase after stroke. Patients are naïve to the hypotheses of the study. Patients and researchers responsible for evaluation of outcomes are blinded to treatment allocation. Figure 1 shows the flow diagram of the trial.

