The proposed protocol will thus provide novel information about the effects of RPSS as an add-on intervention to motor training, under a protocol adapted to a developing-world environment, with shorter duration of treatment sessions, distributed over a longer period of time. Furthermore, the protocol has other differences in comparison to the paradigm applied by previous studies: (11, 46) first, recurrent strokes are included in the present protocol but were excluded by others (11, 46). Recurrent strokes are more common in developing countries such as Brazil compared to developed countries, and represented the most common reason for exclusion (45%) in a prior study of neuromodulation in stroke rehabilitation in Brazil (47). Because this protocol intended to be applied in a developing country, recurrent strokes were not excluded.

Second, while Carrico et al. (11) and Yadav et al. (46) administered RPSS to the Erb's point to provide brachial plexus stimulation, in addition to the median and radial nerves, in the current protocol RPSS is administered to the median, radial and ulnar nerves on the wrist/arm as previously reported (33). RPSS with Erb's point stimulation had not been described when the current protocol was designed, while nerve stimulation on the wrist/arm had been previously shown to be well-tolerated (10).

Follow-ups will continue up to 3 months post-treatment in the current protocol, providing information about long-term duration of effects of RPSS as an add-on intervention to treatment. Also, the evaluation of outcomes at 3 weeks aims to investigate whether 9 sessions of treatment lead to similar effects, compared to 18 sessions of treatment. If this hypothesis is proven correct, larger multicenter studies could be conducted faster, and at lower costs. According to current standards of payment of rehabilitation therapy and interventions of non-invasive peripheral stimulation in public health services in Brazil (http://sigtap.datasus.gov.br/tabela-unificada/app/sec/inicio.jsp), the costs of the entire treatment would be approximately 700 Brazilian reals (or 155 dollars).

Finally, detailed imaging data, including DTI analysis, is used in the proposed protocol in order to characterize the degree of involvement of the corticospinal tract, key to motor recovery after stroke, (48) in both the active and sham groups.

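### No adverse-event question is specified after treatment ends at week 6, and the session questions have no stated recall period, so later events may be under-ascertained in both arms

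*Protocol article*

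**What the plan says.** The Adverse Events section gives two routes for collecting events. The solicited route is "Questions about adverse events are asked immediately after each session of RPSS and FES". The unsolicited route is "Subjects are also instructed to spontaneously report any adverse events throughout the protocol". The Data and Safety Monitoring Plan then covers grading (Common Toxicity Criteria as guidance) and reporting to the Ethics Committee and the NIH. It names no further point at which patients are asked.

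The treatment is wider than stimulation. Under Motor Training each session includes 45 min of task-specific training, and "subjects are assigned 10 functional tasks to be performed daily at home with the paretic arm, for at least 30 min per day". The Outcome Measures section places assessments at weeks 3, 6, 10 and 18, with those at weeks 3 and 6 on days without treatment. The Discussion adds: "Follow-ups will continue up to 3 months post-treatment in the current protocol". Under Interventions, a missed session prompts a call to "ascertain reasons for the absence and reinforce the importance of adherence to the protocol".

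**The concern.** The article fixes a collection rule, and that rule stops when the sessions stop. Two things follow.

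- **After week 6.** No session takes place, so no solicited question is specified. Any event then has to be volunteered, even though the patient is seen at weeks 10 and 18.
- **Weeks 0 to 6.** The questions come directly after stimulation and carry no recall period. If staff take them to mean reactions to the stimulation just given, then problems from training, home practice or the days between sessions are not asked about.

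The Discussion says that the RPSS equipment is not yet approved for clinical use in Brazil or the United States, and that the trial is meant to inform larger studies. As written, solicited data can support a statement about tolerability around the sessions. They are a weak basis for any statement about harms over the full 18 weeks.

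**Working it through.** The article gives no adverse-event rate or reporting probability. The check is therefore schedule arithmetic followed by a comparison of the planned contacts.

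**Inputs**
- Number of sessions (Design): "we compare the effects of 18 sessions of active and sham RPSS as add-on interventions to FES and task-specific training".
- Frequency (Introduction): "distributed three times a week, over 6 weeks".
- RPSS (RPSS section): "In both groups, the duration of stimulation is 90 min".
- FES: 5 min of familiarization plus 25 min.
- Motor training: 45 min per session.
- Last assessment: week 18.

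**Step 1: the plan's own figures.** Sessions: 3 per week × 6 weeks = 18, as stated. Follow-up: 18 − 6 = 12 weeks, which agrees with the stated 3 months after treatment.

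**Step 2: share of the observation period with no solicited question.** 12 / 18 = 0.67, or 67%. Two scheduled visits (weeks 10 and 18) fall inside this period.

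**Step 3: spacing during treatment.** 7 days / 3 sessions = 2.3 days on average between questions. If each question covered the time since the last contact, the treatment period would be well covered up to the last session. If each covered only the stimulation just given, the intervals would not be covered. The text supports neither reading over the other.

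**Step 4: the part of the package with no question of its own.** Session length is 90 + 5 + 25 + 45 = 165 min, and training is 45 / 165 = 27% of it. Over 18 sessions, training is 18 × 45 min = 13.5 h. Home practice is at least 42 × 30 min = 21 h if done every day for 6 weeks, which is an assumption. These hours describe exposure. They do not measure events missed and should not be used that way.

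**Step 5: contacts side by side**

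| Contact | Adverse-event question stated? |
|---|---|
| After RPSS and FES, 18 sessions | Yes; recall period not stated |
| Week 3 and 6 assessments (non-treatment days) | None stated |
| Missed-session call | Reason for absence asked; no stated link to event recording |
| Week 10 and 18 assessments | None stated |
| Any other time | Spontaneous report only |

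The gap after week 6 holds on either reading of the session question, because no later session exists to carry it.

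**The case against.** The strongest case against has five parts.

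1. **Treatment period.** Patients are asked about three times a week with no stated limit on recall, so a later session's question may pick up earlier events. A session of RPSS and FES could also mean the whole visit, training included; the figure of the experimental paradigm is not available to settle this. After each session patients are also asked whether the hand is worse, better or unchanged (Randomization, Allocation Concealment and Blinding). This stands. A reader might infer that training, home practice and the days between sessions rely wholly on volunteered reports; the text does not go that far.
2. **Size.** A reader might also infer that late harms are undercounted. With no event rates given, only a risk of under-ascertainment is supported.
3. **Other safeguards.** The later visits include spasticity, strength, range of motion and depression measures that can show worsening, and the missed-session call does ask for a reason. This stands in part: neither is described as adverse-event collection.
4. **Blinding rule.** It would be wrong to read the limit on what patients may discuss as a bar to reporting harm. It covers their experience during the interventions, and only with outcome assessors and other subjects.
5. **Condensed article.** The full protocol may specify questions at follow-up visits. That is possible, but the article sets out a specific schedule with spontaneous reporting as its only supplement, so the point rests on what is written.

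**Conclusion.** The point holds in a limited form. As written, solicited questioning ends with the last session, leaving 12 of 18 weeks (67%) to spontaneous reports despite two scheduled visits. Within the 6 treatment weeks the defect is an undefined recall period, and coverage there could be good or poor depending on how the question is put.

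The consequence is possible under-ascertainment of events after treatment, and perhaps between sessions, by an amount that cannot be computed from the article. The schedule is the same in both arms, so no bias between arms is evident from it; what is at risk is the completeness of the counts. A low count should not be presented as evidence of safety over 18 weeks. The conclusion assumes that the Adverse Events section describes the whole of the solicited collection.

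**What to change.** In the Adverse Events section:

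- State that the existing session question covers everything since the last contact, including training and home practice.
- Ask the same scripted question at the week 3, 6, 10 and 18 visits and in every missed-session call.
- Report events by arm and by period, with solicited and spontaneous reports shown separately.
- At assessment visits, have the question asked after outcome testing by existing staff other than the blinded assessor. Active RPSS is applied to the arm and sham to the leg, so the site of a symptom could reveal allocation. This matters most at week 6, when the primary outcome is rated.

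The cost is slightly more form work at contacts that already take place, plus a staff member other than the assessor for a few minutes at four visits. More minor events will be recorded, so the rates will look less favourable.
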